In 2013, the Philippines, considered an LMIC, had an overall diabetes prevalence of 6.0%, an estimated 1.7 million people with undiagnosed diabetes, and 54,535 diabetes-related deaths [6]. The Philippines is estimated to have over 6 million people with diabetes by the year 2035 [1]. The Philippines has begun implementation of the World Health Organization Package of Essential Noncommunicable Disease Interventions for primary care settings in low resource areas [7], created the National Centre for Disease Prevention and Control in 2000 including a diabetes-specific office, and has listed reduction of mortality and morbidity from lifestyle-related diseases such as diabetes as one of the goals in the “National Objectives for Health 2005-2010” [8]. However, there are currently some gaps in the areas of detection and treatment for diabetes. For example, though screening kits and medications are available at no cost, the case detection for new cases of diabetes is poor, the diabetes registry is poorly maintained, and the medications often get left unused in the stockrooms of local health centres ([name], Philippine Department of Health, personal communication, June 16, 2014). Knowledge about diabetes is also a gap in the Philippines; in a study in one region of the Philippines the mean score for diabetes knowledge among people diagnosed with diabetes was only 43% [9].

The Cardiovascular Health Awareness Program (CHAP) intervention model may be particularly suited to LMICs due to its low cost, implementability, and focus on population-based health promotion and disease prevention. CHAP is a community-based, primary care-centred, volunteer-led, free of charge, cardiovascular disease risk assessment and blood pressure monitoring program, which is combined with health education sessions for community-dwelling older adults [10]. A large community cluster randomized controlled trial in Canada demonstrated that the CHAP intervention resulted in a statistically significant 9% reduction in annual hospital admissions due to stroke, heart failure, and heart attacks in people aged 65 and over at the population [11]. The CHAP has been successfully expanded to include a diabetes risk assessment component in the Community Health Awareness of Diabetes (CHAD) program and other community adaptations [12, 13].

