### Design

This study is a 26-community parallel open-label cluster randomized controlled trial. A community cluster design was chosen as CHAP-P is intended as a community-level intervention. Potential communities will be stratified by province, population size, income class, and type (urban versus rural). Thirteen barangays will receive the CHAP-P sessions and will be considered intervention communities, while the other 13 communities will receive care as usual and will be considered control communities. This will be done through paired randomization with staggered starts. Communities will be selected and randomized by the local program manager. Criteria for community selection include: security, connection with a local champion, feasibility for travel, and facility with refrigerated space for the HbA1c kits. Barangays will be paired based on municipality, population size, and similarity in the setting (i.e., religion, being under the same health district providing health services, and distance from the municipal centre). This will be done based on the advice of the local health workers and leaders in the municipalities and cities. Allocation will be done by computer generated randomization. Measurements of individual participants will be taken as a repeated cross-sectional sample at baseline and at 6 months. The Pragmatic-Explanatory Continuum Indicator Summary 2 (PRECIS-2) [18] was used to make design decisions based on the pragmatism of the trial (see Fig. 2). Reporting will follow the CONSORT 2010 statement: extension for cluster randomized trials [19]; reporting of this protocol follows the SPIRIT 2013 checklist [20], see Additional file 5.

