### Data collection and management

Community survey participants will be interviewed in their homes by trained research staff at baseline and 6 months. Questionnaires will be completed on paper and later entered into a REDCap [26] database by trained research staff. This survey was adapted from the measure used in the CP@clinic program in Canada [13] and includes questions from other validated questionnaires as well as physical measurements such as blood pressure, height, weight, and waist circumference. The questions include: demographics; knowledge about diabetes and cardiovascular health; risk factors and behaviours, including the Finnish Diabetes Risk Calculator (FINDRISC) [23]; quality of life using the EQ-5D-5 L [24, 25]; perceived confidence; perceived concern and understanding of risk; self-efficacy to improve health behaviours; physical activity using the International Physical Activity Questionnaire (IPAQ) [22]; and health utilization and access. The WatchBP Office Target will be used to measure blood pressure as it was found to show the most reliable results based on our pilot study [27]. This community survey will be completed at baseline and at 6 months and will use an open-cohort design.

After completing the community survey in their homes, these participants will be invited to a community location where they will have their glycated hemoglobin (HbA1c) tested using the A1CNow + point-of-care device, which is certified by the National Glycohemoglobin Standardization Program [28]. HbA1c testing will be conducted at baseline and 6 months, following the community survey at each time point.

Focus group discussions will be held at 6 months for study participants, BHWs, and other LLO staff using a standardized focus group guide consisting of open-ended questions primarily focused on identifying the barriers and facilitators to implementing CHAP-P. Further sources of data include monthly community reports from the communities, monthly observational checklists by research assistants, and record review of the CHAP-P session databases and Rural Health Unit databases.

For CHAP-P session participants, the FINDRISC, blood pressure, and other physical measurement data collected as part of the CHAP-P sessions will be included in the evaluation.

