### Data analysis

#### Quantitative outcomes

The baseline characteristics will be analyzed using descriptive statistics reported by group as mean (standard deviation) or median (first quartile, third quartile) for continuous variables, and count (percentage) for categorical variables. The analysis of all outcomes to compare the groups will follow intention-to-treat principle. We will use multiple imputation to handle missing data. We will use Generalized Estimating Equations (GEE) to make comparisons between intervention and control communities, assuming an exchangeable correlation structure [31]. GEE will allow us to model the correlation of outcomes within communities. All results will be reported as estimates of effect, corresponding 95% confidence interval and associated *p*-values. All p-values will be reported to three decimal places with those less than 0.001 reported as *p* < 0.001. All analyses will be performed using SAS 9.4 (Cary, NC) or Stata 11 (College Station, TX). See Table 2 for the statistical analysis plan.

**Table 2 Tab2:** Statistical Analysis Plan

Research Question	Outcomes and Measures	Participant Group(s)	Time Point	Hypotheses	Method of Analysis
1. What is the difference in HbA1C levels between communities implementing CHAP-P and those not implementing CHAP-P?	• Mean difference in HbA1c (A1C Now+ point-of-care device)	Community survey participants	T_0_, T_6_	Mean HbA1c level will have a greater decrease in intervention communities over control communities	Independent samples t-test (intervention vs control), One-way ANOVA (subgroup analysis), Generalized estimating equations (adjust for clustering effect)

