#### Power and sample size

CHAP-P is a community-wide intervention and community sizes vary from 3000 to 20,000 residents. We are using paired randomization, therefore intervention and control community pairs need to have relatively similar sizes. Our sample size for individuals was calculated based on a mean difference of HBA1c of 0.2% (SD = 1.09) with standard parameters (alpha = 0.05, power = 0.80). This required a sample size of 520 per arm. Based on our pilot, the intraclass correlation coefficient (ICC) was 0.006. We increased our ICC to 0.01 which inflated our sample size to 1034 per arm. We have opted to take 26 (13 pairs of intervention: control) communities with 100 residents per community giving a total sample size of 2600 residents (1300 per arm).

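### The primary HbA1c comparison names adjustment for clustering only; adjusting for age and sex would cost little, gain some precision and give partial protection if participation at 6 months differs by arm.

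*Protocol article*

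**What the plan says.** In the protocol article, Data analysis, Quantitative outcomes: "We will use Generalized Estimating Equations (GEE) to make comparisons between intervention and control communities, assuming an exchangeable correlation structure". The reason given for GEE is the correlation of outcomes within communities. Table 2, which the article presents as its statistical analysis plan, lists three methods for the HbA1c question: an independent-samples t-test, ANOVA for subgroups, and GEE with clustering as the only adjustment named. No participant-level covariate is mentioned, and none is ruled out.

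On sampling, the Design section says "Measurements of individual participants will be taken as a repeated cross-sectional sample at baseline and at 6 months". Data collection and management describes the same survey as an open cohort.

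On available data, Data collection and management says "The questions include: demographics; knowledge about diabetes and cardiovascular health; risk factors and behaviours", and the risk items include FINDRISC.

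On who is measured, Participant recruitment describes systematic household sampling with last-birthday selection. A household with no eligible and willing person is replaced by the next one, and the participant must then go to a community location for the HbA1c test. The trial is open-label, although the article notes that survey respondents may not know their community's allocation.

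**The concern.** If the 6-month sample is drawn afresh, its members have no baseline HbA1c of their own, so the usual strongest covariate is unavailable. Age, sex and diabetes status are the natural substitutes, and the stated model names none of them.

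Two things are at stake. The first is precision: HbA1c varies with diabetes status, and leaving a strong predictor out widens the interval. The second is case mix. By 6 months the intervention communities have had twice-monthly sessions with risk scoring and referral. Agreeing to the survey and then travelling for the test are both voluntary. If people with known diabetes take part more or less readily in one arm, part of the estimated difference would reflect who was measured. Pairing on area-level factors cannot correct that, and neither can baseline community means, because such selection would arise after the program starts.

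**Working it through.** **The plan's own figures.** Power and sample size gives a "mean difference of HBA1c of 0.2% (SD = 1.09) with standard parameters (alpha = 0.05, power = 0.80"), then "This required a sample size of 520 per arm". The pilot value reported is that "the intraclass correlation coefficient (ICC) was 0.006", raised to 0.01 for planning.

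- Two-sided formula: 2 × (1.96 + 0.8416)² × 1.09² / 0.2² = 467 per arm. The stated 520 is reached only with an allowance of about 10% (467/0.90 = 519) that the article does not mention. This does not affect the present point.
- Design effect: 1 + 99 × 0.01 = 1.99, and 520 × 1.99 = 1034.8, which matches the stated 1034.

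**Precision of the unadjusted comparison** (13 communities of 100 per arm, ICC 0.01, SD² = 1.1881):

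- SE = √[2 × (0.01 × 1.1881 + 0.99 × 1.1881/100) / 13] = √[2 × 0.02364/13] = 0.0603.
- Power for 0.2: 91% (normal) or 89% (t, 24 df), above the planned 80%.

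**What adjustment for known diabetes could gain.** The article gives neither the share of residents aged 40 and over with known diabetes nor the HbA1c gap, so both are assumptions.

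- Low end of the share: the Background says the country "had an overall diabetes prevalence of 6.0" per cent, which is overall prevalence, not diagnosed. The same section gives 45.8% undiagnosed globally, so 6.0 × (1 − 0.458) = about 3.3% known. The figure at age 40 and over may be higher; the range runs to 12%.
- Gap: 1.5 to 2.0 percentage points.
- Share of individual variance explained: R² = p(1 − p) × gap² / 1.1881.
- Individual part of the variance of a community mean: 0.0099 / (0.01 + 0.0099) = 0.497.
- Cut in variance of the arm difference = 0.497 × R², with between-community variance left unchanged.

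| Known diabetes | Gap | R² | Variance cut | SE cut | SE |
|---|---|---|---|---|---|
| 3.3% | 1.5 | 0.060 | 3.0% | 1.5% | 0.0594 |
| 6% | 1.5 | 0.107 | 5.3% | 2.7% | 0.0587 |
| 6% | 2.0 | 0.190 | 9.4% | 4.8% | 0.0574 |
| 12% | 2.0 | 0.356 | 17.7% | 9.3% | 0.0547 |

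If the covariate also explained between-community variance, the gain would be larger: for R² = 0.20 the SE would be 0.0539 rather than 0.0572.

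**Chance imbalance.** At 6% prevalence, and applying the HbA1c design effect to diabetes status, the SE of the arm difference in prevalence is √(2 × 0.06 × 0.94 × 1.99/1300) = 0.0131. The 95% range is ±2.6 points, which moves the HbA1c estimate by about ±0.04 to ±0.05. This variation is already part of the outcome variance and hence of the SE of 0.0603.

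**Differential participation.** Each percentage point of arm difference in known diabetes caused by selection moves the estimate by 0.01 × gap = 0.015-0.02, or 7.5-10% of 0.2. The documents give no figure for how large such a difference might be.

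**The case against.** The strongest objection is that this rests on silence. A covariate list is commonly left to a full analysis plan, and the clustering note in Table 2 may only explain why GEE stands beside the t-test. It is true that covariates are not excluded, and a fuller plan may name them. What remains is that the table offered as the analysis plan names one adjustment only, while usable covariates are already collected.

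Three stronger readings are tempting and are not supported.

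- A reader might infer that case-mix differences bias the primary estimate. Communities are paired and randomized by computer, and households are sampled systematically. Chance imbalance is therefore covered by the interval. Bias would require participation to differ by arm; the design permits that, but nothing in the article shows it.
- A reader might infer that nobody at 6 months has a baseline HbA1c. That follows from a repeated cross-section, but under an open cohort some participants would have one.
- A reader might infer that the trial is short of power without covariates. At ICC 0.01 it is not.

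A further objection concerns diabetes status as a covariate. A pre-program diagnosis reported at 6 months is reported after a program meant to raise awareness and detection, so recall could differ by arm and adjustment could introduce bias. This stands, and it is why that variable should not enter the primary model unless recorded beforehand.

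**Conclusion.** The point holds as a modest, inexpensive improvement on the stated method. The planned comparison is valid, but it gives up some precision and has no covariate protection if participation differs by arm. Under the assumed 3-12% with known diabetes and a gap of 1.5-2.0 points, the variance of the arm difference would fall by about 3-18% and its SE by about 1.5-9%. That is the gain from adjusting for diabetes status itself. Age and sex, which are safe to use in every case, would gain less, and would correct differential participation only as far as it runs through age and sex. The size of any such selection cannot be estimated from the article.

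**What to change.** - Adjust the primary GEE for age and sex, and report the unadjusted estimate alongside.
- Pre-specify a sensitivity analysis that adds self-reported diabetes diagnosed before the pair's program start. Use this variable in the primary model only where it was recorded before the program began.
- Do not adjust for diagnoses made during the program, since it aims to increase detection.
- Reconcile the repeated cross-section in Design with the open cohort in Data collection and management. This decides whether any participant's own baseline HbA1c is available as a covariate.

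The cost is a few sentences of analysis wording, slightly more analysis, and possibly one survey question on date of diagnosis. The remaining weakness is that a diagnosis date reported after an awareness program may be recalled differently by arm, so the sensitivity analysis should be read with that in mind.

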**Methods:**

Six-month, 26-community (13 intervention, 13 control) parallel cluster randomized controlled trial in Zamboanga Peninsula, an Administrative Region in the southern Philippines. Criteria for community selection include: adequate political stability, connection with local champions, travel feasibility, and refrigerated space for materials. The community-based intervention, CHAP-P sessions, are volunteer-led group sessions with chronic condition assessment, blood pressure monitoring, and health education. Three participant groups will be involved: 1) Random sample of community participants aged 40 or older, 100 per community (1300 control, 1300 intervention participants total); 2) Community members aged 40 years or older who attended at least one CHAP-P session; 3) Community health workers and staff facilitating sessions. Primary outcome: mean difference in HbA1c at 6 months in intervention group individuals compared to control. Secondary outcomes: modifiable risk factors, health utilization and access (individual); diabetes detection and management (cluster). Evaluation also includes community process evaluation and cost-effectiveness analysis.

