### Outcomes

#### Primary outcome and measure

The primary outcome is the mean difference in HbA1c at 6 months in a random sample of individuals from the random sample of individuals from the intervention barangays compared to the control barangays. HbA1c will be tested at a community location at baseline and 6 months, after the participants have completed the community survey in their homes.

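### The primary contrast is stated two ways, as HbA1c at 6 months and as a greater decrease from baseline, and the documents do not settle which is more precise

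*Protocol article*

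**What the plan says.** The abstract (Methods) states: "Primary outcome: mean difference in HbA1c at 6 months in intervention group individuals compared to control". The section Primary outcome and measure agrees: "The primary outcome is the mean difference in HbA1c at 6 months in a random sample of individuals", comparing intervention with control barangays. Table 2, research question 1, lists T0 and T6 as the time points and gives the hypothesis as "Mean HbA1c level will have a greater decrease in intervention communities over control communities". The methods in that row are a t-test, one-way ANOVA for subgroups, and GEE for clustering. Neither the row nor the text says whether the analysed variable is the 6-month value or the change.

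Baseline HbA1c is collected: "HbA1c testing will be conducted at baseline and 6 months, following the community survey at each time point" (Data collection and management).

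The sampling over time is described in two ways. Design says "Measurements of individual participants will be taken as a repeated cross-sectional sample at baseline and at 6 months". Data collection and management says "This community survey will be completed at baseline and at 6 months and will use an open-cohort design".

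Power and sample size uses a "mean difference of HBA1c of 0.2% (SD = 1.09", alpha 0.05, power 0.80 and an ICC of 0.01 (0.006 in the pilot), with 13 communities of 100 residents per arm.

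**The concern.** Under randomisation the two contrasts have the same expected value, but they are not the same estimator. With 26 communities, chance baseline differences between arms can be appreciable, and the two analyses can then give different estimates and p-values. As the article stands, either could be presented as the planned primary analysis, and nothing in it closes that choice before the data are seen.

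Only the 6-month version appears to have been powered. A calculation for change would need the correlation between baseline and follow-up, or an SD stated to be that of change. Neither is given.

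**Working it through.** **Inputs from Power and sample size.** Difference 0.2; SD 1.09; m = 100 per community; k = 13 communities per arm; ICC 0.01 (pilot 0.006); alpha 0.05, taken as two-sided.

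**Assumed, because the article gives no value.** CAC, the correlation of a community's true mean between baseline and 6 months: 0.5 to 1. IAC, the within-person correlation for anyone measured twice: 0.7. f, the share of people measured twice: 0, 0.5 or 1. Total variance is taken as equal at both times, and pairing is ignored unless stated.

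**The plan's own figure.** Design effect = 1 + 99 × 0.01 = 1.99, and 520 × 1.99 = 1034.8, which matches the stated 1034. The 520 does not follow from the stated inputs alone: they give 467 (468 with a t reference), and 468/0.9 = 520 would need an unstated 10% allowance. This does not affect the present point. No baseline-to-follow-up correlation enters the calculation.

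**Formulas.** Let r be the correlation between a community's baseline and 6-month sample means:

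r = [m × ICC × CAC + f × (1 − ICC) × IAC] / [1 + (m − 1) × ICC]

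Variance relative to the 6-month comparison: change 2(1 − r); baseline-adjusted 1 − r². Change is therefore less precise exactly when r < 0.5. Since 1 − r² = (1 − r)(1 + r), the adjusted factor never exceeds 1 or 2(1 − r). The factor treats the slope as known; estimating it costs one degree of freedom.

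**6-month comparison, ICC 0.01.** SE = 1.09 × √(2 × 1.99/1300) = 0.0603. Noncentrality 0.2/0.0603 = 3.32. Power on 24 df is 88.9%.

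**Fresh samples at each time (f = 0), ICC 0.01.** Here r = CAC/1.99.

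| CAC | r | Change: factor | Change: power, 24 df | Adjusted: factor | Adjusted: power, 23 df | Adjusted: power, 11 df |
|---|---|---|---|---|---|---|
| 1 | 0.503 | 0.995 | 89.0% | 0.747 | 95.6% | 93.6% |
| 0.8 | 0.402 | 1.196 | 82.9% | 0.838 | 93.4% | 90.8% |
| 0.5 | 0.251 | 1.497 | 73.9% | 0.937 | 90.7% | 87.6% |

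The 11 df column is for regressing the 13 pair differences at 6 months on the 13 pair differences at baseline (13 − 2 = 11), with no gain credited to pairing. Change drops just below 80% at a CAC of about 0.7 (79.8%).

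**Fresh samples, pilot ICC 0.006.** The 6-month comparison has 94.4% power. The change factor is 1.247, 1.398 and 1.624 at CAC 1, 0.8 and 0.5, with power of 88.9%, 85.2% and 79.7%.

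**Some or all people measured twice, ICC 0.01, IAC 0.7.**

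| f | CAC | r | Change: factor | Adjusted: factor |
|---|---|---|---|---|
| 0.5 | 1 | 0.677 | 0.647 | 0.542 |
| 0.5 | 0.8 | 0.576 | 0.848 | 0.668 |
| 0.5 | 0.5 | 0.425 | 1.149 | 0.819 |
| 1 | 1 | 0.851 | 0.298 | 0.276 |
| 1 | 0.8 | 0.750 | 0.499 | 0.437 |
| 1 | 0.5 | 0.599 | 0.801 | 0.641 |

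With full overlap, change is more precise than the 6-month comparison throughout this range. With half overlap it depends on CAC.

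**The case against.** The best defence is that Table 2 contradicts the outcome section less than it seems. The research question in that row concerns a difference in HbA1c levels, no change score is named, and the hypothesis may be loose directional wording. The outcome itself is defined consistently in two other places, both contrasts target the same expected effect, and an unseen SAP may already fix the analysis. Part of this stands: the difference lies mainly in the estimator, and the SAP may resolve it. But the row lists both time points and states its hypothesis as a comparison of decreases, so the article's text still needs to be made consistent.

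A reader might infer that a change analysis simply loses power. The documents do not support that. It holds for fresh samples at the pilot ICC, and at ICC 0.01 when CAC is below 1. At ICC 0.01 and CAC 1 it is neutral, and under an open cohort with substantial overlap it can reverse.

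A reader might also take the lack of a named baseline covariate as an error. Covariates are commonly left to an SAP or full protocol, so adjustment is an improvement to recommend. Finally, that the sample size is for the 6-month comparison is an inference from its form: the article does not say whether 1.09 is the SD of levels or of change.

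**Conclusion.** The point holds as an inconsistency in the primary contrast: a 6-month difference in the abstract and outcome section, a difference in change in Table 2. The article does not show which is more precise, because it also describes the sampling in two ways. With fresh samples at ICC 0.01, choosing change moves power from 88.9% to between 89.0% and 73.9% over CAC 1 to 0.5. With everyone measured twice and a within-person correlation of 0.7, its variance is 0.298 to 0.801 of the 6-month variance.

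These figures rest on assumed CAC, IAC and overlap, and on ignoring pairing. They do not show that the trial is underpowered: the 6-month comparison exceeds 80% at both ICCs, and change falls below 80% only when community means correlate fairly weakly over six months. Baseline adjustment is at least as precise as either version under both sampling readings, apart from one degree of freedom.

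**What to change.** 1. State one primary estimand in the abstract, the outcome section and Table 2: mean HbA1c at 6 months, intervention minus control.
2. Reword the Table 2 hypothesis to a lower mean HbA1c at 6 months in intervention communities, and label the difference in change as supportive.
3. Recommended: estimate the primary contrast with the community's baseline mean HbA1c as a covariate. It needs no linkage of individuals, so it works under either sampling reading. In an analysis by pairs, regress the 6-month pair difference on the baseline pair difference.
4. Reconcile Design with Data collection and management: say whether the 6-month survey draws a fresh sample, re-measures the same people, or mixes the two.

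The cost is wording plus one degree of freedom. HbA1c is already measured at baseline, so no new data are needed.

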2. What is the difference in modifiable lifestyle risk factors between communities implementing CHAP-P and those not implementing CHAP-P?	• Physical activity (IPAQ) • Medication compliance (self-report, survey question) • Blood pressure (BP; WatchBP Office Target device) • Risk factors for diabetes (FINDRISC) • Risk Behaviours for Diabetes / Cardiovascular Issues (activity, diet, smoking, alcohol, stress; self-report, measured with elements of the Health Awareness and Behaviour Tool [HABiT]) • Knowledge about Diabetes and Hypertension (self-report; measured with elements of the HABiT) • Perceived Concern and Understanding of Risk (self-report; measured with elements of the HABiT) • Confidence in Behaviour Change (self-report; measured with elements of the HABiT)	Community survey participants (all outcomes) CHAP-P session participants (change in BP over time; diabetes risk score)	*Survey* T_0_, T_6_ *Session* BP: each session Diabetes risk score: T_0_, T_6_	In intervention versus control communities, physical activity, medication compliance, knowledge, perceived concern and understanding of risk, and confidence in behaviour change will have more of an increase, blood pressure, diabetes risk score, and risk behaviours will have more of a decrease In CHAP-P session participants, blood pressure will decrease with more length of time involved in the program; diabetes risk score will decrease pre to post.	Independent samples t-test (intervention vs control), One-way ANOVA (subgroup analysis), Generalized estimating equations (adjust for clustering effect), Hierarchical linear modelling (BP over time)

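### For research questions 1 and 2, Table 2 lists a t-test and a one-way ANOVA that ignore the randomized communities beside GEE, the method named in the text; the table should make GEE the sole inferential comparison

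*Protocol article*

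**What the plan says.** Under Quantitative outcomes, the protocol article says that GEE with an exchangeable correlation structure will be used to compare intervention and control communities, and adds that "GEE will allow us to model the correlation of outcomes within communities". It then refers the reader to Table 2 for the statistical analysis plan.

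The Method of Analysis entries in Table 2 differ by research question:

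- **Question 1 (HbA1c, the primary outcome):** "Independent samples t-test (intervention vs control), One-way ANOVA (subgroup analysis), Generalized estimating equations (adjust for clustering effect").
- **Question 2 (lifestyle and risk-factor outcomes):** "Independent samples t-test (intervention vs control), One-way ANOVA (subgroup analysis), Generalized estimating equations (adjust for clustering effect), Hierarchical linear modelling (BP over time").
- **Question 3 (diagnosis, treatment initiation, admissions, mortality, and the two survey items on access to care):** GEE only, in linear and Poisson form.

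The section Power and sample size plans for clustering: "We increased our ICC to 0.01 which inflated our sample size to 1034 per arm". The pilot value is also given: "the intraclass correlation coefficient (ICC) was 0.006".

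**The concern.** Communities are randomized, so residents of one community cannot be treated as independent replicates of their arm. An independent-samples t-test on residents does exactly that. Its standard error is too small, its interval too narrow, and its p-value too often below 0.05. In Table 2 this test carries the intervention-versus-control label, while GEE is described only as adjusting for clustering. Neither entry is marked as decisive or descriptive.

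The same section says that results will be reported with confidence intervals and p-values. A t-test and a GEE result for the same outcome can disagree, and the table does not say which would be quoted.

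The ANOVA raises a separate issue. A one-way ANOVA compares means over the levels of a single factor. It does not assess whether the effect of CHAP-P varies between subgroups, and it too ignores the communities.

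**Working it through.** **Inputs, all from Power and sample size:** 13 communities per arm, m = 100 residents per community, 1300 per arm; planning ICC 0.01; pilot ICC 0.006; "standard parameters (alpha = 0.05, power = 0.80"). Sidedness is not stated, so two-sided is assumed. The t-test is taken as a comparison of individual HbA1c values at 6 months.

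**1. The plan's own design effect.** DE = 1 + (m − 1) × ICC = 1 + 99 × 0.01 = 1.99. Then 520 × 1.99 = 1034.8, which agrees with the stated 1034 apart from rounding. The plan therefore works with a design effect of 1.99.

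The starting figure is a side matter. The plan says "This required a sample size of 520 per arm" for a "mean difference of HBA1c of 0.2% (SD = 1.09"), but 2 × [1.09 × (1.960 + 0.842) / 0.2]² gives 467 per arm. This has no bearing on the present point, because the error rate below depends only on ICC and community size.

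**2. Understated standard error.** The true standard error is √DE times the one the t-test uses: √1.99 = 1.41 at ICC 0.01, and √1.594 = 1.26 at ICC 0.006 (DE = 1 + 99 × 0.006 = 1.594).

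**3. Actual two-sided type I error of a nominal 5% t-test:** 2 × [1 − Φ(1.96 / √DE)].

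| ICC | DE | Formula | Simulation |
|---|---|---|---|
| 0.006 (pilot) | 1.594 | 12.1% | 12.0% |
| 0.01 (planning) | 1.99 | 16.5% | 16.5% |

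The simulation used 200,000 runs of 13 against 13 communities with 100 residents each.

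**4. Allowance for pairing.** Barangays are randomized in pairs. If outcomes of paired communities correlate by r, the between-community part of the variance of the arm difference shrinks by the factor (1 − r): DE = 1 − ICC + m × ICC × (1 − r). The article does not give r, so the values below are assumptions.

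| r (assumed) | Type I error, ICC 0.006 | Type I error, ICC 0.01 |
|---|---|---|
| 0 | 12.1% | 16.5% |
| 0.3 | 9.9% | 13.2% |
| 0.5 | 8.5% | 10.8% |
| 0.8 | 6.3% | 7.2% |

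The rate stays above 5% in every row.

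**5. ANOVA.** The article names no subgroups and no factor, so no error rate can be computed. The point is one of method: a difference in effect between subgroups is an arm-by-subgroup interaction, and a one-way layout has no such term.

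**The case against.** The strongest reply is that the text settles the matter. GEE is the only between-arm method named in the prose, it stands in the same table cell as the t-test, and no part of the article calls the t-test primary. A natural reading is an unadjusted look at the data followed by the cluster-adjusted comparison. Most of this stands. A reader who sees only the t-test entry might infer that the primary analysis ignores clustering, or that the trial's conclusion carries a 16% false-positive rate. The article does not support either reading: the inflation reaches the conclusion only if the t-test is used for inference.

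Three further limits are fair. The t-test is not listed for all survey outcomes, because the access-to-care items under question 3 are assigned to GEE. The 16% figure rests on an ICC deliberately set above the pilot value and takes no credit for pairing. Details of subgroup analyses are often left to a fuller plan.

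The reply does not remove the mismatch. The table is presented as the statistical analysis plan, attaches the between-arm label to the t-test, and does not call it descriptive. A t-test on the 26 community means would respect the clusters, but nothing indicates that this is meant: the participant column lists survey participants, and only GEE is tied to clustering. Question 3 shows that the authors could specify GEE without the other two tests.

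**Conclusion.** The point holds as a conflict between table and text, limited to research questions 1 and 2. Two of the listed methods do not suit a trial that randomizes communities, and the table does not say that GEE governs. Used for inference on residents, the t-test would have a two-sided type I error of about 12% to 16% across the plan's two ICCs, before any gain from pairing. This assumes 100 analysed residents per community and a two-sided 5% level. With assumed within-pair correlations up to 0.8 the rate falls as low as 6.3%, still above nominal. The planned GEE comparison is not affected. The ANOVA is the wrong tool for a subgroup question about the intervention, but the size of that problem cannot be determined from the article.

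**What to change.** In Table 2, for research questions 1 and 2:

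- Delete the independent-samples t-test, or mark it as descriptive with no p-value or confidence interval.
- State that the cluster-adjusted GEE is the sole inferential comparison between arms, in line with the text and with question 3.
- Replace the one-way ANOVA with an arm-by-subgroup interaction in the same cluster-adjusted model, reporting the interaction test and the subgroup-specific effects.

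The cost is a few words in one table, settled before analysis. No new data are needed, the sample size is unaffected, and the GEE estimates and intervals stay as planned.
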